### Ethics Statement

This research project was approved by the Regional Ethics Committee for Medical Research Ethics, Western Norway (2011/1877). Written consent is collected from all participants.

All sensitive data (digital and non-digital) generated are confidential and will be treated according to the standards set by the Norwegian Data Inspectorate (Datatilsynet) and in compliance with the Health Research Act and the Personal Data Act.

### Equipment

Location: Salvation Army Treatment Center Stavanger, Rogaland, Norway.

Watch (Polar M200, M360), weight scale, stopwatch, chair, running track (Stavanger Stadium), exercise sling, two gym mats, computer for neurocognitive testing, and a timer (Tabata).

## Stepwise Procedures

Recruitment and eligibility. Patients will be recruited from the Helse Vest catchment area via the subacute treatment facility FAB. The Helse Vest catchment area consist of western Norway. FAB is mainly recruiting form the county of Rogaland and the main cities in the region Stavanger, Sandnes, and Haugesund. The patient target group for FAB is refered patients from the specialized health care system, with an addiction so serious that inpatient treatment is deemed necessary by a evaluation center. Comorbidity of light psychiatric diagnoses are accepted. We included patients of 18 years of age and upward. The patients often receive social benefits or disability pension. Education among the patient group is mixed from elementary school to university educated. We included patients mixed between first time rehabilitation to varying number of previous admission. Eligibility: SUD diagnosis, admitted as an inpatient to FAB; ≥18 years of age; passes the physical evaluation for the institution to perform intensive training; no medical history or illness that precludes participation in physical activity; and psychiatric diagnoses no more serious than the grading of light to moderate. Patients will be excluded from the study if their medical history (e.g., physical disability, disease, or injury) could interfere with or be exacerbated by physical activity. For example, patients with paralysis, severe pain, obstructive disease, glaucoma, or who are unable to sit, stand, and/or walk will be excluded, as well as patients with a severe cognitive deficit, such as dementia. A severe cognitive deficiency will be assessed based on the patients’ responses to two questions: “Do you have trouble with your memory that affects your daily life?” and “Have you been given a medical diagnosed of dementia?” Protocol deviations: If participants are absent from more than 60% of the training sessions. They are considered protocol violators. If they are not able to participate at allocated test times and complete the tests, they are considered protocol violators. They are still included in the study and tested as soon as possible. Statistical analyses will be performed both based on the principle of “intention to treat” including everyone regardless of protocol violation and “per protocol” analyses will be performed, comparing only those that have completed the protocol.

1.Baseline testing. The physical and neuropsychological testing will be conducted within 2 weeks of admittance to the Salvation Army Treatment Center.2.The researchers will not conduct randomization, as there is natural allocation as a result of the SUD treatment allocation system, which will be continuous throughout the study.3.The control group is completed first. Structure is changed in the clinic and intervention group is started up after the last control patient has left the clinic.4.The intervention will consist of the physical exercise protocol, which will be conducted for 4 weeks.5.The final tests of physical function will be conducted the week after the exercise protocol is completed. The prospective follow-up will consist of cognitive testing carried out at 3, 6, 9, and 12 months after the baseline test.6.Discontinuation: Patients that don’t follow the protocol or don’t follow the TAU of the Facility will be discontinued. If they don’t complete the follow up test with in the allocated time line or neglect to perform the test they will be discontinued (Figure 1).

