## Introduction

Substance use disorders (SUD) are among the most prevalent, chronic, and severe diseases in the world in terms of mortality and disability (Kessler et al., 2007), and they are associated with considerable social, economic, and individual health consequences (Adrian and Barry, 2003; Schuckit, 2006; Hasin et al., 2007; Kirby and Sugden, 2007; Wittchen et al., 2011). The combination of impaired physical and mental health among SUD populations is associated with life expectancies that are 20–30 years less than the general population (Stenbacka et al., 2010; Nordentoft et al., 2013). Individuals with SUD have a high tendency for comorbidity. Compared with the general population, the SUD group has more frequent contact with the healthcare system (Richards et al., 1999, 2017; Bernstein et al., 2014) because of a variety of illnesses such as cancer, diabetes, cardiovascular diseases, different kinds of physical trauma, and suicide (Kim et al., 2009; Stenbacka et al., 2010; Nordentoft et al., 2013). Depression, anxiety, attention deficit hyperactivity disorder (ADHD), personality disorder, and psychosis are among the most common comorbidities (Conway et al., 2006; Pennay et al., 2011; Pettinati et al., 2013; Adida et al., 2014; Harstad et al., 2014; Hartz et al., 2014). Individuals with SUD also have a high prevalence of cognitive impairment, which can contribute to low quality of life and the tendency to drop out of treatment (Rosselli and Ardila, 1996; Gouzoulis-Mayfrank and Daumann, 2006; Hagen et al., 2016, 2017a,b, 2019; Topiwala et al., 2017; Hall et al., 2018). A recent study (Hagen et al., 2016) also highlighted the importance of adequate recovery time for cognitive functions. Although pharmacological and psychological interventions are well established in the treatment and the research fields, relapse rates are typically high. The limited success rates of SUD treatments provide a good argument for focusing on adjunct treatments for SUD patients with interventions that target both physical and mental health.

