However, only a few studies have examined the impact of physical activity or exercise in patients with SUD (Zschucke et al., 2012; Giesen et al., 2015). In September 2017, we conducted a literature search in Embase, Medline, SPORTDiscus, PsycINFO, and CINAHL using the search terms “high-intensity interval training” (HIIT), “high-intensity circuit training” (HICT), “cognitive function,” and “SUD.” The results of our search yielded 11 articles (Weinstock et al., 2008, 2014; Smith and Lynch, 2011; Wolff et al., 2011; Zschucke et al., 2012, 2013; Flemmen et al., 2014; Wang et al., 2014; Haglund et al., 2015; Klika and Jordan, 2015; Unhjem et al., 2016) of relevance to this study. This corpus included research that examined physical activity for SUD populations as outpatients or inpatients in recovery after withdrawal (Zschucke et al., 2012). Physical activity or exercise for SUD populations was shown to improve physical fitness, cardiovascular health, and sleep quality, and reduce the withdrawal symptoms of substance use, as well as anxiety and depression symptoms (Roessler, 2010; Zschucke et al., 2012; Wang et al., 2014; Giesen et al., 2015; Hallgren et al., 2017). It has also been observed that engaging in a physical activity program during treatment can contribute to reduced dropout rates, thereby increasing the success rate of therapy (Weinstock et al., 2014). Although this body of work presents promising results, many of the studies have methodological limitations, such as being pilot studies or lacking control groups. Because of the positive impact exercise can have on mental health, we believe it is extremely important to explore exercise interventions in the clinical treatment and recovery for SUD populations. Preexisting data and approaches in the field of mental health and SUD show great promise; for example, HIIT principles have been found to increase health benefits (Milanović et al., 2015; Unhjem et al., 2016; Karlsen et al., 2017). However, we lack data on dose, intensity, and the most beneficial types of exercise.

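### The per-protocol set excludes patients for late or incomplete tests as well as for missed training, so it also selects on outcome attendance

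*Protocol article*

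**What the plan says.** All references are to the protocol article.

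- **Stepwise Procedures, Protocol deviations** gives two grounds for being a violator. The first concerns training: "If participants are absent from more than 60% of the training sessions". The second concerns testing: "If they are not able to participate at allocated test times and complete the tests, they are considered protocol violators". The second names no visit and no time window.
- The same paragraph says of violators: "They are still included in the study and tested as soon as possible". It plans an intention-to-treat analysis of everyone and a per-protocol analysis "comparing only those that have completed the protocol".
- **Stepwise Procedures, step 5** schedules a physical test in the week after the programme and "cognitive testing carried out at 3, 6, 9, and 12 months after the baseline test".
- **Stepwise Procedures, step 6** says that patients who miss the follow-up test timeline, or do not perform the test, are discontinued.
- **Control Group** and **Intervention Group**: only the intervention group has the exercise sessions, four a week. **Physical Exercise/Intervention Protocol** sets both the control and the intervention period at 4 weeks.
- **Anticipated Results** plans a linear mixed model that allows for missing data where there are three or more measurements.

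**The concern.** A per-protocol analysis is meant to describe the effect in patients who received the treatment as intended. Turning up on time for a cognitive test months after a 4-week programme says nothing about how much of it was received. It belongs to the process by which the outcome is observed.

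The article's own background gives reason to think that this filter is not neutral. The Introduction says that cognitive impairment is common in this population, "which can contribute to low quality of life and the tendency to drop out of treatment", and that "engaging in a physical activity program during treatment can contribute to reduced dropout rates". Both remarks concern staying in treatment, not attending later research tests, so carrying them over is an inference. It is a reasonable one: attendance may depend on cognition and on group. If so, restricting to complete attenders makes the two groups less comparable, on top of the sequential, non-randomised allocation. It also discards patients from a trial with 30 per group.

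The exclusion is also unnecessary, because the planned mixed model can use patients with incomplete test series.

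**Working it through.** **1. Is there a figure in the plan to reproduce?** No. The article gives no expected size for the per-protocol set and no attendance or dropout rate. Under Limitations it says only that dropout was high in previous studies. Its power statement (0.8 with at least 10 per group) concerns fitness and depression scores and gives no effect size, so it does not bear on this point.

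**2. What each rule tests.**
- Training rule: 4 sessions × 4 weeks = 16 sessions, and 60% of 16 = 9.6. Missing 10 or more is a violation, so a patient who attends 7 of 16 (44%) passes.
- Test rule: no limit is stated. Applied to all of step 5, it covers five post-baseline occasions (one physical, four cognitive).
- Read together, a patient with 16 of 16 sessions and a missed 9-month test is a violator. One with 7 of 16 sessions and every test on time is not.
- For controls the training rule is empty, which leaves only the test rule. Step 6 adds adherence to usual treatment, but as a ground for discontinuation.

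**3. How many would be kept?** *Assumption:* each test is on time and complete with probability p, independently, and no one is lost on the training rule. Share kept over k tests = p^k; number kept = 30 × p^k.

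| p | k = 4: share | of 30 | k = 5: share | of 30 |
|---|---|---|---|---|
| 0.9 | 0.656 | 19.7 | 0.590 | 17.7 |
| 0.8 | 0.410 | 12.3 | 0.328 | 9.8 |
| 0.7 | 0.240 | 7.2 | 0.168 | 5.0 |

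With k = 4, the share falls below half when p < 0.5^(1/4) = 0.841. With k = 5, the limit is 0.5^(1/5) = 0.871.

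**4. Sensitivity to clustering within patients.** Attendance is unlikely to be independent.
- Beta-binomial model with intra-patient correlation 0.3 and k = 5: shares of 0.729, 0.519 and 0.358 for p = 0.9, 0.8 and 0.7. Times 30, that is about 22, 16 and 11.
- Logistic model with a shared patient-level stability factor (log-odds 1.0 per SD) and k = 4: about 21, 14 and 10 of 30.

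Clustering keeps more patients, but makes those kept a more distinct subgroup.

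**5. Precision.** The 95% half-width for a standardised difference is about 1.96 × √(2/n).
- n = 30: 0.51
- n = 20: 0.62
- n = 12: 0.80
- n = 7: 1.05

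The article treats an effect of 0.5 or more as clinically relevant. These counts use the independence model; under clustering the loss is smaller.

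**6. Bias, as an illustration only.** Take the stability model with k = 4, a correlation of 0.3 to 0.5 between stability and cognition, and no true effect. At p = 0.8, kept patients score about 0.15 to 0.26 SD above the full group. With assumed on-time rates of 70% in controls and 85% with exercise, the per-protocol difference is −0.09 to −0.15 SD, against exercise, because controls are filtered harder. This concerns the *level* of cognition. A stable trait that shifts baseline and follow-up equally cancels in change from baseline, and no calculation was done for change.

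**The case against.** The strongest reply has four parts.

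- **The 12-month reach is inferred.** The deviation rule mentions allocated test times only. The Design section places the one-year follow-up after completion of the trial, and step 5 calls months 3 to 12 prospective follow-up. Completing the protocol could mean the 4-week phase and its tests. *This stands in part:* the literal text has no such limit, but it is not the only reading. Nor does the article say whether one missed test removes a patient from every comparison or only from that visit. Even on the narrow reading, the test just after the programme remains a ground for exclusion, and controls are still judged on testing alone.
- **Treatment received does count.** A reader might infer that the set selects on test attendance in place of treatment received. The documents do not support that: the training rule is also there, and the test rule is added to it.
- **The loss and the bias are assumed.** A reader might infer that well under half of the patients would remain. No attendance rate supports that. Under the stability model, p = 0.8 keeps about 14 of 30, just under half, and it takes p near 0.7 to go well below. The group-specific rates behind the bias are also assumptions, and the result is small beside 0.5. *This stands.*
- **Other analyses protect the trial.** Intention to treat keeps everyone, violators are still to be tested, and a mixed model is planned. *This stands as a limit on the harm.* It is weakened by step 6: if patients who miss the timeline are discontinued and not tested again, intention to treat loses their later data too.

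**Conclusion.** The point holds. The article itself makes late or incomplete testing a protocol violation, alongside the training rule, and limits the per-protocol analysis to completers. That analysis therefore also conditions on attendance at outcome tests, and among the two stated violation criteria this is the only one that can apply to controls. It is a rule that is stated and badly fixed, not a detail left for a later document.

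The size is conditional. Over four follow-up tests, assumed independent on-time rates of 0.9, 0.8 and 0.7 keep about 20, 12 and 7 of 30 per group; within-patient clustering keeps more. The size and direction of any bias in the group difference cannot be settled from the documents. A reader might also infer that recovery is overstated in both groups, but the working shows only that the level of cognition among those kept could be higher.

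The harm is confined mainly to the per-protocol result, since intention to treat is also planned. The change should be made before analysis, but this point does not undermine the trial's intention-to-treat comparison.

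**What to change.** In Protocol deviations, or in the analysis plan:

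1. Separate test deviations from treatment deviations.
2. Define the per-protocol set by treatment received only: training sessions attended in the intervention group and, for controls, the corresponding 4-week treatment period.
3. Remove late or incomplete tests as a ground for exclusion from that set.
4. Analyse all available tests in that set with the planned mixed model, entering late tests at their actual date.
5. Report late and missing tests by group and visit.
6. Reconcile Protocol deviations, which keeps patients with late tests in the study, with step 6, which discontinues them. The reconciled text should make clear that late and subsequent test data are collected and used; otherwise item 4 cannot be carried out. Whether and when treatment itself stops is a clinical matter on which this review takes no position.

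The cost is a few sentences, with no new measurements beyond those already scheduled. The small downside is that patients with incomplete test series stay in the per-protocol set, so its result relies on the mixed model's missing-data assumption.

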## Abstract

This proposed study will examine whether structured physical activity reduces the recovery time of cognitive functioning during the early phase of substance use disorder treatment. Addiction or substance dependence is associated with neurobiological changes and cognitive impairment that can affect quality of life and the efficacy of therapy for up to a year after clinical detoxification. The biological, psychological, and social effects of physical exercise have the potential to be a therapeutic approach to increase quality of life and relieve symptoms associated with substance abuse, such as psychosis, depression, and anxiety. There is a dearth of research on physical activity and exercise in clinical substance use disorder patients. This protocol describes a clinical study that will examine cognitive recovery after substance abuse using physical exercise as a treatment intervention. We will use a quasi-experimental longitudinal clinical trial, with a pretest and multiple posttests, on naturally randomized sequential groups. Patients will be consecutively be recruited into the study groups, with a control group that is completed, before its followed by an intervention group, each with 30 patients. Patients will be enrolled 2 weeks after the start of detoxification, at which time all subjects will be inpatients at the Stavanger Salvation Army Treatment Center in the Norwegian specialized healthcare system. Cognition will be evaluated with a comprehensive battery of cognitive tests, including several tests of executive function. Physical fitness will be tested with the Rockport 1-Mile Walk Test, the 30-S Chair Stand Test, the 1-Min Burpee Test at baseline (within the first 2 weeks of admittance) and after 4 weeks. The intervention will be a 30-min workout at 70–90% of maximum heart rate (134–170 bpm), recorded and calculated by a Polar heart rate monitor. The intervention treatment will be administered four times a week for 4 weeks and will consist of high-intensity circuit training, high-intensity interval training, functional movement, and primitive reflex training. We anticipate improvement in both the control and intervention groups, with the exercise intervention group having the greatest increase in recovery of cognitive function because of the combination of functional full body movements and primitive movement training in an intense interval training program.

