## Anticipated Results

In this study, we expect the participants in both the control and intervention groups to show progress in physical and mental health after a period of substance abuse. We believe that the data generated in this project will mostly be at the interval or ratio level (whether the rating of perceived exertion is ordinal or interval data will not be discussed here). We will use the mean as a measure of central tendency for the group results for the neurocognitive test, while the reflexes we use frequency and proportions, and the standard deviation to express the spread of results within the group. If useful, the standard error of the mean (SEM) will be used to express the accuracy of the mean value. If the results are highly skewed (skewness > 1.5), we will use a log transformation and geometric mean together with a 95% confidence interval to express central and spread tendencies. To compare results over time from pretest to posttests, and between-group differences, we will use repeated measures ANOVA/*t*-tests with Sidak/Holm *post hoc* tests, where we have collected three or more measurements a linear mixed modeling accounting for the missing data will be used. Group comparisons will be made with an ANOVA/*t*-test for independent groups. If the test of normality should fail (Kolmogorov–Smirnov with Lilliefors correction), the corresponding non-parametric tests will be used, i.e., the Wilcoxon–Mann–Whitney rank sum test for independent *t*-tests and repeated measures ANOVA for ranks (Tukey’s *post hoc* test). Statistical significance will be set at a *p*-value of ≤0.05, and effect sizes will be calculated according to Cohen (1988), with the help of an online effect size calculator (the CEM effect size calculator, Center for Evaluation and Monitoring, Durham University, United Kingdom^1^). An effect size of ≥0.5 will be considered clinically relevant (two-sided). If there is a need for building indexes of different types of scores, *Z*-scores will be used. Based on previously published data on fitness development and depression scores, we should be able to attain statistical power of 0.8 with at least 10 subjects in each of the two groups. Nevertheless, we have set target recruitment at *n* = 30 for each group.

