### Limitations of the Study

Because the intervention and control groups will be run consecutively rather than concurrently, there is the potential for non-equivalent time periods to create bias. However, we chose this approach because previous studies had suffered recruitment failures and high dropout rates. The length of the proposed study is not fixed, and because of our funding and support, this study can continue until the quota for participants is met.

This study is designed to accommodate clinical realities. Thus, different SUD groups are not fractionated during treatment, and the project protocol does not divide different groups of SUD after clinical classification. This may create some problems with the results from baseline because of various issues with the abuse of different drugs and possible side effects that might affect the test results differently. We will account for this Statistically.

Finally, the patient population will be recruited straight out of a detoxification clinic, which will most likely influence the test results. However, this may actually be an advantage, because having access to patients so quickly after controlled, medically supervised detoxification may give us a more accurate picture of their mental status when the patients are at their lowest point in their recovery trajectories.

The Norwegian Ministry of Health and Social Affairs and the Salvation Army of Norway have provided financial support for this study.

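### Baseline cognition may be tested on any day in the first 2 weeks of admission and the stated analyses carry no timing term, so unequal timing between the sequential cohorts could bias the comparison of change in either direction

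*Protocol article*

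**What the plan says.** - **Testing window.** Stepwise Procedures: the physical and neuropsychological baseline tests "will be conducted within 2 weeks of admittance" to the treatment centre. No target day is set. The Abstract gives the same 2-week window for the fitness tests.
- **Enrolment.** Abstract: "Patients will be enrolled 2 weeks after the start of detoxification". This dates enrolment, not the baseline test.
- **State of the patients.** Limitations of the Study: patients come directly from detoxification and are assessed "when the patients are at their lowest point in their recovery trajectories".
- **Order of the cohorts.** Stepwise Procedures: "Structure is changed in the clinic and intervention group is started up after the last control patient has left the clinic". Cohort and treatment are therefore the same variable.
- **Follow-up.** Stepwise Procedures: "cognitive testing carried out at 3, 6, 9, and 12 months after the baseline test".
- **Analysis.** Anticipated Results: group comparisons use ANOVA or a t-test "for independent groups", with rank tests as a fallback and a linear mixed model where three or more measurements exist. No covariate is named. A standardised effect of 0.5 is taken as clinically relevant, and the target is 30 patients per group.
- **Acknowledged bias.** The limitations section concedes that consecutive cohorts may bring bias from non-equivalent periods, but offers no analytic remedy. Its promise of a statistical adjustment concerns the different drugs of abuse.

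**The concern.** The trial asks whether exercise speeds cognitive recovery, so the point on the recovery curve at which each patient is first measured matters. That point can vary by up to 2 weeks between patients, in a phase the article itself describes as the bottom of the curve.

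In a randomised concurrent trial such variation would be noise. Here the cohorts are separated in calendar time and the clinic is reorganised between them, so a difference in scheduling would fall entirely along the treatment contrast. A cohort tested earlier starts lower on the curve. If recovery is steepest at the start, that cohort shows more change over the same follow-up interval with or without exercise. Earlier testing of the intervention cohort would flatter exercise; earlier testing of the control cohort would hide an effect. The analyses as described cannot separate this from treatment.

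**Working it through.** **Inputs from the article.** Baseline window 0 to 14 days after admission; first cognitive follow-up 3 months (taken as 13 weeks) after the baseline test; 30 per group; two-sided significance level 0.05; relevance threshold 0.5. The article gives no recovery rate, no SD and no timing data, so there is no figure of its own to reproduce on this point.

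**Assumptions.** Mean cognition t weeks after admission, without exercise, follows f(t) = −D·exp(−t/τ). The deficit at admission is D = 0.5 or 1.0 SD and the time constant is τ = 4, 13 or 26 weeks. The SD of change is 1. There is no true exercise effect.

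**Formula.** With baseline at week b, change to 3 months is

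f(b + 13) − f(b) = D·exp(−b/τ)·[1 − exp(−13/τ)].

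If one cohort is tested at week b₁ and the other later, at b₀, the false difference in change (earlier minus later cohort) is

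D·[exp(−b₁/τ) − exp(−b₀/τ)]·[1 − exp(−13/τ)].

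**Worked case: D = 1.0, τ = 4.**
- 1-week mean shift (days 3.5 and 10.5, so b₁ = 0.5, b₀ = 1.5): (0.8825 − 0.6873) × (1 − 0.0388) = 0.1952 × 0.9612 = 0.188 SD.
- Full 2-week shift (days 0 and 14): (1 − 0.6065) × 0.9612 = 0.378 SD.

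**All scenarios.** The rejection rate is the chance of a significant two-sided t-test on change with no true effect, from the noncentral t distribution. The last column is the difference if only the 3-month scores are compared.

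| D (SD) | τ (weeks) | Bias in change, 1-week shift | Rejection rate | Bias in change, 2-week shift | Rejection rate | 3-month score only, 1 / 2 weeks |
|---|---|---|---|---|---|---|
| 0.5 | 4 | 0.094 | 0.065 | 0.189 | 0.111 | −0.004 / −0.008 |
| 0.5 | 13 | 0.023 | 0.051 | 0.045 | 0.053 | −0.013 / −0.026 |
| 0.5 | 26 | 0.007 | 0.050 | 0.015 | 0.050 | −0.011 / −0.022 |
| 1.0 | 4 | 0.188 | 0.110 | 0.378 | 0.302 | −0.008 / −0.015 |
| 1.0 | 13 | 0.045 | 0.053 | 0.090 | 0.064 | −0.026 / −0.052 |
| 1.0 | 26 | 0.015 | 0.050 | 0.029 | 0.051 | −0.022 / −0.045 |

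Against the 0.5 threshold, the largest 1-week bias is 0.188 / 0.5 = 38% and the largest 2-week bias is 0.378 / 0.5 = 76%.

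**Linear recovery.** If f(t) = r·t, change is r·(b + 13) − r·b = 13r for every b. The bias in change is exactly zero, because the interval from baseline is the same for everyone.

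**The case against.** Five points on the other side deserve weight.

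1. **Follow-up is dated from the baseline test.** A reader might multiply a daily recovery rate by the shift in days: 3 days at 0.01 SD up to 7 days at 0.03 SD gives 0.03 to 0.21 SD. At a constant rate that product is wrong, since elapsed time is equal in both cohorts and the bias in change is zero. A constant 0.03 SD per day would also imply 0.03 × 91 = 2.7 SD of natural recovery in 3 months. The product is approached only if recovery is fast in the window and nearly complete by follow-up. This stands, and the sizes above therefore come from curves that slow down.

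2. **The t-test is not the only stated analysis.** Cognition has five time points, so the mixed model applies to it. This stands. The article names no timing term for either analysis, so the point covers both.

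3. **Covariates are commonly left to the analysis plan**, which is not shown and may contain one. True, and the article does not rule out adjustment. The point is confined to what the article fixes: an open testing window, non-concurrent cohorts, and a group comparison named without adjustment.

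4. **A shift is conjecture.** The same window governs both cohorts, and a change in clinic structure says nothing direct about test scheduling. This stands: the risk is conditional.

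5. **The enrolment rule and the testing window are not in conflict.** One might read the Abstract's 2 weeks from the start of detoxification as contradicting the 2 weeks from admission. They date different events on different clocks. Neither fixes the test day, but there is no contradiction.

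**Conclusion.** The point holds as a conditional one. The window, the early-recovery phase, the sequential cohorts and the absence of a timing term in the stated analyses are all in the text. A bias in change follows only if mean timing differs between cohorts and recovery decelerates. Under the assumed curves it is about 0.01 to 0.19 SD at 3 months for a 1-week mean shift and at most 0.38 SD for the full 2 weeks, in either direction. It raises the rejection rate to about 0.1 or more only with the fastest recovery (τ = 4 weeks) and a mean shift of at least a week. If 3-month scores alone are compared, it is at most about 0.05 SD.

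A reader might infer that a scheduling shift would pass as an exercise effect. The documents do not support that: they show no shift, the direction is unknown, and no scenario reaches 0.5 SD through timing alone. This is an inexpensive safeguard worth adding, not a defect that invalidates the comparison. Recovery depth, time constant and SD of change are all assumptions.

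**What to change.** - In the between-group analysis of every cognitive outcome, including the mixed model, add two covariates: days from admission (or from the start of detoxification, where recorded) to the baseline test, and the baseline score. In the mixed model, take the follow-up scores as the response. If baseline stays in the response, a main effect for days moves all visits equally and leaves change unadjusted.
- Tabulate days to the baseline test by cohort. If the distributions match, the table itself answers the concern.
- Confirm that admission and test dates are recorded for every patient. The article's timing rules imply this but do not state it.

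**Cost.** About two degrees of freedom. If timing turns out to be strongly associated with cohort, the adjusted comparison loses some precision, because the two are then hard to separate.
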